#### Sample size calculation

We calculated the sample size using the statistic software SAS (SAS Institute GmbH, Heidelberg, Germany). This study has an explorative character and is supposed to deliver first-ever data. There is currently no comparative data available for the medication group or time intervals considered. For the control group regimen, there is data available from a previous study [22] for two time points (60 min and 120 min after exposure). Therefore, we considered the deviation of [A^−^] at the time point T5 (120 min) compared to baseline T1 (0 min) applying a *t* test. We expect normally distributed data since the control group data derived from the previous study showed the same characteristics [22]. We set the level of significance to 5% and the power to 80% resulting in 21 patients per group. With the addition of swix patients for the pilot phase, the total number of patients is 48.

#### Analysis procedure

The primary objective of the study is to show that during the observation period of 120 min the mean values of [A^−^] display a lower deviation in the treatment group when compared to the control. We will evaluate normal distribution using the Kolmogorov-Smirnov test. To test for differences between two study groups with normally distributed data, a two-sample *t* test will be used. In order to evaluate differences of [A^−^] within one study group over time, we will perform a RM-ANOVA with a *t* test for paired samples as post hoc. We will analyse data that does not follow a normal distribution using the Friedman test. Level of significance for all calculations is defined at 5%. We will analyse secondary parameters descriptively and calculate mean, number, minimum, maximum, 1st quartile, 3rd quartile, mean standard error and standard deviation (SD) (method of aggregation: continuous). Further analyses and testing procedures can be defined at a later stage. The primary statistical analysis is based on the “intention-to-treat” principle. Safety data (UE, SUE, SUSARs) will be analysed descriptively in all groups at least every 12 months.

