### Statistical evaluation

#### Power considerations

This study aims to show that [A^−^] can be stabilized by applying IMP1/IMP2 in a combined approach. In a previous investigation of our group, [A^−^] was reduced by 2.67 ± 2.4 mmol/l in patients who had received 4000 ml of Jonosteril® over 120 min [22]. We expect that we can counteract the decrease in [A^−^] up to 60% when using the IMP1/IMP2 protocol. This will presumably result in an average difference in [A^−^] of 1.602 mmol/l in the treatment group. Furthermore, we assume that [A^−^] will be more stable over all time points. As a consequence, the range of [A^−^] will be lower in the treatment compared to the control group. Therefore, we expect that the standard deviation will rather be 1.8 mmol/l than 2.4 mmol/l (estimated reduction of 30%) [22].

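### The primary between-group test ignores the T1 [A⁻] value measured in every patient; it is valid, but an analysis adjusted for T1 would probably be more efficient

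*Protocol article*

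**What the plan says.** All references are to the protocol article.

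- **Test.** Analysis procedure: "To test for differences between two study groups with normally distributed data, a two-sample" *t* test will be used. Repeated-measures ANOVA is reserved for changes over time within one group. The sentence does not name the variable to be tested.
- **Sizing variable.** Sample size calculation takes the deviation of [A⁻] at T5 "compared to baseline T1 (0 min) applying a" *t* test. That the primary test is on change is inferred from this sentence.
- **Sample size.** "We set the level of significance to 5% and the power to 80% resulting in 21 patients per group".
- **Assumptions.** Power considerations: in the earlier study [A⁻] "was reduced by 2.67 ± 2.4 mmol/l in patients who had received 4000 ml" of the control solution. The decrease is to be counteracted "up to 60% when using the IMP1/IMP2 protocol", giving an average difference "of 1.602 mmol/l in the treatment group". The "standard deviation will rather be 1.8 mmol/l than 2.4 mmol/l (estimated reduction of 30"%).
- **Baseline.** The Randomization phase section defines T1 (0 min) as baseline, and Table 1 lists [A⁻] at T1–T5. No section names T1 [A⁻] as a covariate.
- **Endpoint wording.** Primary endpoint describes a deviation from a reference of around 15 meq/l, which is not the change from T1 used for sizing.

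**The concern.** A two-sample *t* test on T5 minus T1 forces the slope of T5 on T1 to equal 1. If the true slope is lower, as dilution and measurement error would tend to make it, subtracting the whole baseline adds noise. A chance difference between the arms at T1 then also shifts the observed change difference, by (slope − 1) × that difference. ANCOVA estimates the slope and removes both effects. Allocation is simple and unstratified with about 21 patients per arm, and T1 is already collected, so the plan leaves information unused. What is at stake is precision in a trial sized at barely 80% power. Bias and type I error are not at stake.

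**Working it through.** **Inputs from the article:** difference 0.6 × 2.67 = 1.602 mmol/l; SD 1.8 mmol/l; alpha 5%; power 80%; 21 per group. Sidedness is not stated ("Level of significance for all calculations is defined at 5"%). Two-sided is assumed because one-sided testing would need only 17 per group.

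**Step 1: reproduce the plan's figure.**
- Normal approximation: n = 2 × (1.96 + 0.8416)² × 1.8² / 1.602² = 19.8, so 20 per group.
- Exact noncentral *t*: 20.82, so 21 per group.
- Power at 21: noncentrality = 1.602 / (1.8 × √(2/21)) = 2.884 on 40 df, giving 0.803.

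The stated 21 is therefore consistent with an unadjusted two-sample *t* test using SD 1.8 in both arms.

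**Step 2: variance under ANCOVA.** Let σ be the common SD at T1 and T5 and rho their correlation.
- Variance of the change: 2σ²(1 − rho).
- Residual variance of T5 given T1: σ²(1 − rho²).
- Ratio: (1 − rho²) / [2(1 − rho)] = (1 + rho)/2.
- Residual SD: 1.8 × √((1 + rho)/2).
- Implied SD at T1: 1.8 / √(2(1 − rho)).

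**Step 3: power with 21 per arm.** ANCOVA has 42 − 3 = 39 df and a variance penalty for chance baseline imbalance of 1 + 1/(42 − 4) = 1 + 1/38. Noncentrality = 1.602 / (residual SD × √((2/21) × (1 + 1/38))). At rho 0.5 this is 1.602 / (1.559 × 0.3126) = 3.287.

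| rho (assumed) | Variance ratio | Residual SD | Implied SD at T1 | ANCOVA power | n per arm for 80% |
|---|---|---|---|---|---|
| 0.5 | 0.75 | 1.559 | 1.8 | 0.893 | 17 |
| 0.7 | 0.85 | 1.660 | 2.3 | 0.853 | 19 |
| 0.8 | 0.90 | 1.708 | 2.8 | 0.833 | 20 |
| 0.9 | 0.95 | 1.754 | 4.0 | 0.813 | 21 |
| 0.95 | 0.975 | 1.777 | 5.7 | 0.803 | 21 |
| limit: change unrelated to T1 | 1.00 | 1.800 | – | 0.793 | 22 |

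The comparator throughout is 0.803 for the *t* test on change.

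**Step 4: simulation.** With 42 patients, simulated ANCOVA power was 0.89, 0.85 and 0.82 at rho 0.5, 0.7 and 0.9 (20,000 runs each). Type I error stayed near 5% for both methods.

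**Step 5: robust standard errors.** These matter if unequal variances are a concern, since the plan expects less spread in the treatment group. The simulation used equal SDs of 1.8 at rho 0.5 and 0.8.
- HC0 with normal critical values: type I error about 7%.
- HC3 with *t* critical values: type I error about 4%, and at rho 0.8 power of about 0.81, which loses most of the gain.
- HC1 with *t* critical values: type I error about 5%, and power 0.89 and 0.83, matching ordinary ANCOVA.

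**The case against.** The strongest reply is that nothing here is an error. A *t* test on change is unbiased under randomization and keeps its type I error, and the sample size matches it. The article calls the study explorative and allows further analyses to be defined later. All of that stands and limits the point to efficiency. It does not remove the point: the article itself names the primary test, so this is a stated choice, and permission for later analyses does not plan an adjusted primary one.

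The second reply is that the gain rests on a correlation the article does not give. This also stands. The gain shrinks as rho rises and turns into a small loss above about 0.95. It would also vanish if T5 were more variable than T1, so that the slope came close to 1. Adjustment is free in patients and measurements but costs one degree of freedom.

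A reader might infer three stronger claims that the documents do not support:
- **That starting [A⁻] varies widely, which makes adjustment more valuable.** The article gives no between-patient SD for [A⁻]. With the change SD held at 1.8, a larger SD at T1 implies a higher rho and a smaller gain.
- **That true power is already below 80%.** On the stated inputs it is 0.803. With SD 2.4 in both arms it would be 0.56, but whether 1.8 is a defensible SD is a separate question.
- **That baseline imbalance passes in full into the comparison.** That would apply to raw T5 values or a signed deviation from 15. The sizing text points to change from T1, where only the fraction (1 − slope) passes through, and without bias on average.

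**Conclusion.** The concern holds as a matter of efficiency. The planned test is valid and its sample size reproduces, but it leaves a measured baseline unused. With 21 per arm, change SD 1.8 and equal SDs at T1 and T5, ANCOVA would raise power from 0.80 to between 0.81 and 0.89 for rho between 0.9 and 0.5. There is no gain from rho about 0.95, and the worst case is a loss of about one percentage point, to 0.79. Break-even would need a between-patient SD of about 5.7 around a mean near 15. A positive gain is therefore the more plausible outcome, though its size is an assumption. The change is worth making; leaving it out would not invalidate the trial.

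**What to change.** 1. Settle the primary variable. Primary endpoint (deviation from about 15 meq/l) and Sample size calculation (T5 relative to T1) must be reconciled first. ANCOVA of T5 on T1 matches the sizing variable. It gives the same treatment estimate for T5, T5 − T1 or a signed T5 − 15, but it does not test an absolute deviation from 15 or stability over all time points.
2. Before data are analysed, prespecify as primary an ANCOVA of T5 [A⁻] on treatment with T1 [A⁻] as covariate, reporting the adjusted difference and its 95% CI.
3. If unequal variances are a concern, name a small-sample robust variance with *t* critical values, for example HC1 with a *t* reference. A general reference to robust errors is not enough with 21 per arm.
4. Keep the two-sample *t* test on T5 − T1 as a sensitivity analysis.

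Cost: no extra patients, samples or visits, and one degree of freedom. Step 1 is a substantive decision and not just wording. Because the trial is open-label and already recruiting, it should be made and documented without sight of outcome data by arm.

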## Outcome measures

### Primary objective

The primary objective is to compare two infusion therapy regimes, Jonosteril® + Sodium glycerophosphate (IMP1/IMP2) versus Jonosteril® (IMP1) alone, with the aim to demonstrate superiority of IMP1/IMP2 over IMP1 due to a more stable value of [A^−^] during the observation period of 120 min after the initiation of general anaesthesia.

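### If the normality check fails, the superiority objective has no valid stated test, because the Friedman test compares times within patients and not arms

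*Protocol article*

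**What the plan says.** The aim is a comparison between arms. The Primary objective section compares the two regimens "with the aim to demonstrate superiority of IMP1/IMP2 over IMP1", on the ground of a more stable [A⁻] over 120 minutes. The Analysis procedure section restates this as showing that mean [A⁻] values "display a lower deviation in the treatment group when compared to the control".

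That section then sets four rules:

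1. A normality check: "We will evaluate normal distribution using the Kolmogorov-Smirnov test".
2. A between-arm test for normal data: "To test for differences between two study groups with normally distributed data, a two-sample *t* test will be used".
3. An analysis of change over time: "within one study group over time, we will perform a RM-ANOVA with a *t* test for paired samples as post hoc".
4. A rule for everything else: "We will analyse data that does not follow a normal distribution using the Friedman test".

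No rank-based test for two independent groups, no group-by-time interaction and no joint model of both arms is named. The section adds that more tests may be specified later. The Sample size calculation section expects normal data, and it sizes the trial on the deviation of [A⁻] at T5 from T1 with a t test.

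**The concern.** Only rule 2 contrasts the arms, and it applies only when normality is accepted. Rule 4 takes over when it is not, and it names a test for a different question. Friedman asks whether [A⁻] differs between time points in the same patients. It can be strongly significant when the two regimens perform identically, and silent when they differ.

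The primary comparison is at stake. If the check rejects, the team must either report a test that does not bear on superiority or choose a between-arm test after seeing the data. The trial is open-label, so a choice made at that point would be hard to defend as prespecified.

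**Working it through.** **1. The plan's own figure.** Inputs from Power considerations and Sample size calculation: difference 1.602 mmol/l (60% of 2.67), SD 1.8, alpha 5%, power 80%.

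- Standardised difference: 1.602 / 1.8 = 0.89.
- Normal approximation: n per arm = 2 × (1.960 + 0.842)² / 0.89² = 19.8, so 20.
- Noncentral t: 20.82, so 21 per arm, with power 0.803 at 21.
- A one-sided test would need only 17.

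The stated 21 per group is thus reproduced by a two-sided, between-arm, two-sample t test. The trial was sized for the contrast that rule 4 does not deliver.

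**2. Two readings of the Friedman sentence.**

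| Reading | Test of the arm contrast if normality is rejected |
|---|---|
| Friedman replaces every test for non-normal data | Friedman, which has no treatment term |
| Friedman replaces only the within-group RM-ANOVA | None named; the t test is limited to normal data |

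On either reading superiority has no valid stated test in this branch.

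**3. Illustration by simulation.** There were 4,000 trials per scenario, with 21 per arm and five time points. Assumptions not taken from the documents: baseline SD 1.5; SD of the T1 to T5 change about 1.8, with 80% of its variance from patient-specific slopes; in the skewed case those slopes follow a shifted exponential. Entries are the proportion of trials with p < 0.05.

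| Mean change (treatment / control) | Friedman, treatment arm | Friedman, control arm | Friedman, arms pooled | Two-sample t | Rank-sum |
|---|---|---|---|---|---|
| Normal: −2.67 / −2.67 (no arm difference) | 1.00 | 1.00 | 1.00 | 0.051 | 0.045 |
| Normal: −1.068 / −2.67 | 0.70 | 1.00 | 1.00 | 0.81 | 0.79 |
| Normal: +0.801 / −0.801 | 0.46 | 0.45 | 0.04 | 0.80 | 0.78 |
| Skewed: −2.67 / −2.67 (no arm difference) | 1.00 | 1.00 | 1.00 | 0.046 | 0.052 |
| Skewed: −1.068 / −2.67 | 0.86 | 1.00 | 1.00 | 0.80 | 0.89 |
| Skewed: +0.801 / −0.801 | 0.34 | 0.73 | 0.10 | 0.82 | 0.90 |

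With no arm difference Friedman rejects almost always. With a true difference of 1.602 in opposite directions, pooled Friedman rejects in 4% of normal and 10% of skewed trials, while the two-group tests reject in about 80 to 90%.

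**4. How often the branch would be entered.** Assumed example of clear skew: lognormal with sigma 0.6, n = 21, standardised by the sample mean and SD.

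- Uncorrected Kolmogorov-Smirnov: rejects in about 4% of samples (3.6% to 3.9% across runs), and in 0% of normal samples.
- Lilliefors-corrected: rejects in about 47% (45% to 47%), and in 4.5% of normal samples.

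The plan does not say which version is meant.

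**5. Price of a rank-based check.** Dividing 20.82 by the rank-sum test's efficiency under normality (0.955) gives 21.8, so 22 per arm. Dividing by its lower bound for shift alternatives (0.864) gives 24.1, so 25. At 21 per arm the simulated power is about 0.79 under normality.

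**The case against.** **The expected route does test superiority.** The protocol expects normal data, names a two-sample t test for them, and sized the trial on that test. This stands. A reader might infer that superiority is never tested at all; the document does not support that.

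**The Friedman sentence may concern only the within-group analysis.** It follows the RM-ANOVA sentence directly, and Friedman is the usual rank counterpart. The reading is plausible, so it cannot be stated as fact that Friedman replaces the t test. But the sentence carries no such limit, and on this reading the arm comparison still has no test for non-normal data.

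**A missing fallback is detail for an analysis plan.** Silence would be. Here the protocol restricts the t test and affirmatively names an unsuitable test for the remaining data. Room to add tests later does not correct that.

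**The RM-ANOVA is not at fault.** A reader might infer that superiority will be claimed because one arm changed significantly and the other did not. The plan never says so: it assigns this analysis to change "within one study group over time, we will perform a RM-ANOVA". On the plan's figures the paired T1 to T5 test would be significant with probability 0.735 under treatment (t = 1.068 / (1.8/√21) = 2.72) and 0.998 under control (t = 2.67 / (2.4/√21) = 5.10). Those figures describe an inference that is not planned. They justify a clarifying sentence, not a charge of error.

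**A normality check at n = 21 may be nearly inert.** That holds for the uncorrected version only. If it is used, the branch is rarely entered and the t test that runs instead is sound: its type I error was 4.8% in 10,000 simulated trials with two such lognormal arms of 21. With the Lilliefors correction the branch becomes a realistic outcome for skewed data. A general statement that the check cannot detect non-normality is not supported.

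**Conclusion.** The point holds for the non-normal branch and only there. If the Kolmogorov-Smirnov check rejects, no stated procedure validly tests superiority, whichever way the Friedman sentence is read. That conclusion follows from what each test compares and does not depend on the simulation assumptions.

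The probability of reaching the branch cannot be fixed from the document. About 4% against about 47% illustrates how far it turns on the unstated version, for one assumed skewed distribution. If [A⁻] changes are normal, as the protocol expects, the branch is entered in 0% to 4.5% of samples.

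Severity is moderate: the primary comparison is affected, but in a contingency branch, and the repair is simple.

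**What to change.** - Remove the normality check as a gate for the primary comparison. Always compare the arms on [A⁻] at T5 as change from T1, the contrast on which the trial was sized.
- Preferably use ANCOVA with the T1 value as covariate; T1 is already collected. A repeated-measures mixed model with a treatment contrast at T5 is an acceptable alternative, not a requirement.
- Name a Wilcoxon rank-sum or permutation test of the T1 to T5 change as the robustness check.
- State that the RM-ANOVA, the paired t tests and the Friedman test describe change within an arm and are not evidence of superiority.

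The cost is analysis wording only, with no new data. With the rank-sum test as a check, 21 per arm can stay (power about 0.79 under normality). Only if the rank-sum test itself had to reach 80% power would the size rise, by 1 to 4 patients per arm (22 to 25). The change should be made before any outcome comparison is seen.

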#### Data handling and dropouts

INPADS GmbH will perform data management according to the DEGL and DMP. All patients who drop out will be listed, followed-up and monitored. We will document the reason for dropping out and all data registered until then will be included in the analysis. After inclusion of six patients, we will perform an interim analysis. Although dropouts will be very unlikely, due to the design of the study, we will replace the dropout in the case of such an event. Strategies to improve adherence to protocols involve the participation of an investigator (anaesthesiologist) who is responsible for the trial during the initiation of anaesthesia and in the observation period as well as for the completion of checklists in similar format of the CRF. Since patients are under anaesthesia during the intervention, other strategies, such as patient focused techniques, are not intended.

### Ethics and Good Clinical Practice

The trial will be conducted in accordance with the Clinical Trials Directive 2001/20/EC of the European Parliament and of the Council, the International Conference on Harmonization guidance regarding Good Clinical Practice (ICH-GCP E6 R1), the relevant national regulations and the Declaration of Helsinki. Monitoring is independent from the sponsor and competing interests. If external auditing is demanded by an authority, it will be independent from investigators and sponsor. Any modifications to the protocol will be, and have been, immediately communicated to all responsible authorities.

## Discussion

Although there is currently a broad variety of so-called balanced crystalloid preparations available, none of them is ideal and capable of stabilizing the patient’s acid-base balance. This is due to the nature of their composition. Stewart’s concept of acid-base homeostasis may provide a new approach to improve the daily clinical routine of fluid administration. By administering sodium glycerophosphate pre-emptively, it is hypothesized that stable values of [A^−^] can be maintained in patients in the need for larger amounts of fluids due to illness or type of surgery. Furthermore, by supplementing phosphate perioperatively, a frequently occurring hypophosphatemia can be avoided. This trial will increase our knowledge in the applicability of Stewart’s concept of acid-base as well as in the field of perioperative fluid substitution, an area that has a broad applicability in medicine and is directly linked to the patients’ outcome.

### Trial status

Recruiting: participants are currently being recruited and enrolled.

### SPIRIT guidelines

The PALANCE study protocol was written in accordance with the Standard Protocol Items: Recommendations for Interventional Trials (SPIRIT). A completed SPIRIT Checklist (Additional file 1) and a SPIRIT figure (Fig. 2) has been included in this manuscript.

## Abbreviations

AE: Adverse event
ASA: American Society of Anaesthesiologists’ performance status classification system
CRF: Case Report Form
CRO: Contract Research organizations
DEGL: Data entry guideline
DMP: Data management plan
ECG: Electrocardiography
GFR: Glomerular filtration rate
Hb: Haemoglobin
ICU: Intensive care unit
IMP: Investigational medicinal product
ITT: Intention-to-treat
IV: Intravenous
SAE: Serious adverse event
SDP: Sponsor-delegated person
SD: Standard deviation
SUE: Severe unexpected event
SUSAR: Severe unexpected serious adverse event
SVV: Stroke volume variation
UE: Unexpected event
